## Abstract

**Background:** Disulfiram (DSF) is a well-tolerated, inexpensive, generic drug that has been in use to treat alcoholism since the 1950s. There is now independent preclinical data that supports DSF as an anticancer agent, and experimental data suggest that copper may increase its anti-neoplastic properties. There is also some clinical evidence that DSF is a promising anticancer agent in extracranial cancers. In glioblastoma, DSF induced O
^6^-methylguanine methyltransferase (MGMT) inhibition may increase response to alkylating chemotherapy. A recent phase I study demonstrated the safety of DSF in glioblastoma patients when DSF was administered at doses below 500 mg/day together with chemotherapy. We plan to assess the effects of DSF combined with nutritional copper supplement (DSF-Cu) as an adjuvant to alkylating chemotherapy in glioblastoma treatment.

**Methods:** In an academic, industry independent, multicenter, open label randomized controlled phase II/III trial with parallel group design (1:1) we will assess the efficacy and safety of DSF-Cu in glioblastoma treatment. The study will include 142 patients at the time of first recurrence of glioblastoma where salvage therapy with alkylating chemotherapy is planned. Patients will be randomized to treatment with or without DSF-Cu. Primary end-point is survival at 6 months. Secondary end-points are overall survival, progression free survival, quality of life, contrast enhancing tumor volume and safety.

**Discussion:** There is a need to improve the treatment of recurrent glioblastoma. Results from this randomized controlled trial with DSF-Cu in glioblastoma will serve as preliminary evidence of the future role of DSF-Cu in glioblastoma treatment and a basis for design and power estimations of future studies. In this publication we provide rationale for our choices and discuss methodological issues.

**Trial registration: **The study underwent registration in
EudraCT 2016-000167-16 (Date: 30.03.2016,) and Clinicaltrials.gov
NCT02678975 (Date: 31.01.2016) before initiating the study.

## Introduction

Glioblastoma is a highly malignant brain tumor associated with limited treatment responses and population based series report median survival of only 10 months
^1^. Standard initial treatment is extensive surgical resections followed by postoperative fractionated radiotherapy, and concomitant and adjuvant temozolomide treatment. Unfortunately, initial treatment prolongs survival only modestly and in principle all glioblastomas eventually recur
^2^. Initial responses to chemotherapy are more often seen in patients with O
^6^-methylguanine methyltransferase (MGMT) hypermethylation, and consequently this is an important predictive biomarker
^3^. At time of recurrence there is no international treatment consensus
^4,
5^. A common approach is to reintroduce temozolomide as long as the progression occurs more than 3–6 months after end of the initial treatment. In patients with tumor progression early after primary treatment or seen on ongoing temozolomide therapy, lomustine (also known as CCNU)
^6^ or the combination regimen procarbazine, CCNU and vincristine (PCV) are often the treatment of choice. However, effect of second line treatment is often limited and new improved treatments are therefore imperative.

‘Repurposing’ of drugs for new indications has gained increased interest
^7^. Disulfiram (DSF) is an inexpensive, generic drug that has been used since 1947 to treat alcohol dependency
^8^. When alcohol is avoided, the drug is well tolerated in doses below 500 mg daily even with concomitant administration of temozolomide
^9^.

DSF has demonstrated a wide range of antineoplastic effects, potentially also in gliomas
^10–
16^. The interaction of DSF with copper (DSF-Cu) is likely responsible for the anti-cancer effect where DSF-Cu inhibit so-called glioma initiating cells at very low concentrations
^17^. DSF-Cu may further inhibit the proteasome system
^10,
17,
18^ and potentiate alkylating DNA damage through impaired DNA repair in glioma cells, an effect that may be mediated through inhibition of MGMT
^17,
19^. Finally, a recent paper demonstrated benefit of cancer patients using disulfiram and suggested ditiocarb–copper complex to be the metabolite of disulfiram with anti-cancer effects through effects on protein turnover
^20^. As a consequence, it is now suggested that DSF-Cu should be implemented in clinical trials
^17,
21^.

We seek to study the efficacy and safety of adding DSF combined with nutritional copper supplement (DSF-Cu) to patients with recurrent glioblastomas and concomitant with alkylating chemotherapy. The study is an academic, multicenter, open labeled randomized controlled phase II/III superiority trial with parallel group design. The aim of this paper is to present the intervention, design, endpoint, and power calculations of this study.

## Methods and design

### Study design

The study is a multi-center, open label randomized controlled phase II/III trial with parallel group design. All patients receive alkylating chemotherapy, and in the experimental arm treatment with DSF-Cu is added. Patients will be in the study at a maximum of 24 months or until death.

### Participants, interventions and outcomes

***Study setting*.** The patients will be recruited from and treated at University Hospitals in Norway and Sweden. The study involves eight centers (Gothenburg, Stockholm, Linköping, Lund, Jönköping, Uppsala, Örebro and Trondheim). The study was opened for inclusion January 2017 and per October 14 2018 we have randomized 36 patients.

***Eligibility criteria*.** Adult patients (≥ 18 years) with first recurrence of glioblastoma will be screened for inclusion from the regular clinical practice at regional oncological departments (
Figure 1). The full eligibility criteria are presented in
Table 1. In short, adult patients intended for treatment with alkylating chemotherapy for recurrent glioblastoma are eligible if they have a Karnofsky Performance status 60–100 (ECOG Grade 0-2)
^22^, are willing to refrain from alcohol, and have no major contraindications towards DSF-Cu.

**Figure 1. f1:**
[figure not shown]
Flow-chart of patient screening, inclusion and follow-up.

**Table 1. T1:** Full inclusion and exclusion criteria.

Inclusion criteria	Exclusion criteria
Age 18 years or older.	History of idiopathic seizure disorder, psychosis or schizophrenia.
A previous histopathologically verified diagnosis of glioblastoma/ gliosarcoma (later referred to as only glioblastoma) now presenting with a first-time progression/recurrence documented by MRI.	Uncontrolled hypertension (i.e. systolic BP > 180 mmHg) and a diagnosis of congestive heart failure
Planned treatment of recurrence with chemotherapeutic alkylating agents	Received radiotherapy within the 3 months before the diagnosis of tumor progression to reduce risk of misdiagnosis due to pseudoprogression.
Karnofsky performance status of 60 – 100 ^22^.	Addiction to alcohol or drugs.
At inclusion not receiving another experimental treatment, including compassionate use programs, for glioblastoma	Pregnant and/or breastfeeding and women of childbearing potential who do not have a negative pregnancy test taken no longer than 14 days prior to randomization.
Able to take oral medications.	History of liver disease.
No known allergy to DSF or copper.	History of Wilson's disease.
Absolute neutrophil count ≥ 1,500/mcL and platelets ≥ 100,000/mcL	History of hemochromatosis.
Willingness to refrain from ingestion of alcoholic beverages while in the study is a criterion to be randomized. However, once randomized alcohol abstinence only affects the group treated with DSF	Nickel hypersensitivity ^8^
	Need for metronidazole, warfarin and/or theophylline medication since their metabolism may be influenced by DSF.
	Patients who are taking medications metabolized by cytochrome P450 2E1
	Unfit for participation for any other reason judged by the including physician

***Interventions*.** There is no consensus on choice of treatment at first glioblastoma recurrence
^5^. In the Nordic countries, temozolomide, lomustine or PCV are commonly applied. A pragmatic comparator is thus needed to reflect clinical practice. Preclinical data suggest that DSF may enhance the effect of alkylating agents through inhibition of DNA repair
^17^. We therefore use DSF-Cu combination as add-on to “any alkylating chemotherapy” in the intervention group while the comparator group receives “any alkylating chemotherapy” alone.

The administration of DSF and nutritional copper supplement is scheduled to start concomitant with alkylating chemotherapeutic treatment. Patients will take DSF (Antabus
^®^) as a once daily oral dose of 400 mg, based on the known toxicity profile
^9^. In case of intolerance, dose reduction to 200 mg per day is allowed. Copper supplementation will be administered separately from DSF with DSF administration in the evening. Copper nutritional supplement will correspond to 2.5 mg of elementary copper, which is not considered a safety concern
^23^. Adherence to treatment will be assessed at each control with a reminder, self-reporting of drug intake and drug tablet count of remaining DSF. The only surveillance of nutritional copper intake is by self-reporting.

Before study closure no crossover from the control group to DSF-Cu is allowed.

The intervention should continue also after change of chemotherapy, or during temporary chemotherapy withdrawal due to reached maximal cumulative dose or side effects from chemotherapy.

Patients are to discontinue permanently the treatment with DSF-Cu for any of the following reasons:

 Unacceptable adverse effect(s) as judged by the treating doctor. No longer indication for tumor targeted therapy. The patient wishes to withdraw from treatment. If patients develop conditions that contribute to excess risk as judged by the treating physician.

Other experimental therapy, including compassionate use programs, are not allowed in either treatment group as long as the patient is in the trial and receives the assigned treatment.

***Outcomes*.** The primary end-point of the study is survival assessed at 6 months post-randomization.

Secondary end-points are:

 Overall survival from date of randomization. Median progression free survival. 6 and 12 month progression free survival. Health-related generic quality of life
^24^. Volumetric growth rate assessed from baseline MRI to first follow-up MRI scan
^25^. Safety assessment (toxicities).

***Participant timeline*.** To reduce patient burden, timing of data collection after randomization is scheduled according to choice of chemotherapy regimen, where patients that receive temozolomide usually are assessed every 4
^th^ week while patients treated with PCV/lomustine are assessed every 6
^th^ week. Consequently, this may lead to four additional observations in the temozolomide group compared with the lomustine/PCV group. The more detailed clinical control and MRI assessment every 3
^rd^ month is independent of chemotherapy regimen. The primary endpoint will not be affected by the differences in timing of assessments during the trial.

Finally, hematological status and liver function will be monitored as long as patients are on active treatment every 4–6 weeks, once again depending on the chemotherapeutic protocol (
Table 2).

**Table 2. T2:** Schematic view of study schedule with timing and content of study visits.

Visit	Screening	Monthly	Every 3 months
Month *	0	1,2,4,5,7,8,10,11	3,6,9,12,15,18,21,24
Eligibility	X		
Informed consent	X		
Alcohol screen **	X		X
KPS	X	X	X
Demographics	X		
Pregnancy test	X		
Medical history	X		
Euroqol-5D 3L	X		X
Toxicity/AE/SAE/SAR and SUSAR		X	X
Compliance		X	X
Discontinuation		X	X
Consider drug interactions	X		X
MRI Scan	X		X
Blood samples:			
Hematological and liver monitoring ***	X	X	X

AE denotes adverse event, SAE; serious adverse event, SAR; serious adverse reaction SUSAR; suspected unexpected serious adverse reaction, MRI; magnetic resonance imaging, KPS; Karnofsky Performance Status *The interval for patients treated with lomustine/PCV is 6 weeks, while 4 weeks is clinical routine in the case of temozolomide **Continued alcohol screen only relevant if randomized to the disulfiram group. ***Blood samples as indicated here relevant as long as on active treatment and includes: hemoglobin, thrombocytes, leukocytes with differential count, ASAT, ALAT, G-GT, ALP, bilirubin, INR).

***Sample size and study power*.** The sample size calculation is based on data from previous trials reporting that 50% of patients treated with lomustine deceased within 8 months
^6^. We use a phase III end-point in a phase II setting because this study will be the basis for power calculation of a later more rigid phase III study, and because progression is less relevant in patients with already demonstrated progression/recurrence and with a short expected survival. Due to the phase II/III setting we are relaxing the alpha value to 0.10 (by convention 0.05) since phase II studies are “preliminary assessment of a new intervention before embarking on a larger and expensive randomized controlled trial”
^26^. Thus, we argue that it is good science to slightly increase the chance of false positive results (due to chance) for a relevant end-point instead of using less relevant and difficult to interpret surrogate end-points (such as progression).

Based on the assumption that the treatment group will have an improvement in proportion achieving 6-month survival from 60% to 80% we need a final sample size of 128 in total (64 in each group; alpha 0.1, power 80% and two sided test). Considering 10% attrition, the actual included sample need to be 142 with 71 patients included in each group.

***Assignment of interventions*.** A web-based randomization system (WebCRF 3.0) developed and administered by the Unit of Applied Clinical Research, Faculty of Medicine and Health Sciences, Norwegian University of Science and Technology (NTNU, Trondheim, Norway), will be used. Randomizations are computer generated in a 1:1 ratio with stratification by center. Blocks of varying sizes will be used to make prediction of allocation impossible. Randomization will be performed only after the initial chemotherapy treatment has been selected. Patient enrollment is performed by a study member with appropriate delegation at the local site.

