### Data collection, management and analysis

***Data collection*.** Patients will be in the trial for a maximum of 24 months or until death (see study schedule in
Table 2). Generic quality of life is followed every 3
^rd^ month using EQ-5D 3L. Quality of life will be monitored until progression, death or 24 months post-inclusion
^24,
27^.

MRI scanning will be performed at a minimum of every 3
^rd^ month. MRI assessment may continue up to 24 months post-inclusion and this should be implemented also after documented progression in the DSF-Cu group, as long as the patient continues on only DSF-Cu, or in combination with another established rescue therapy such as surgery, radiation therapy or other alkylating chemotherapy. Consequently, MRI controls are indicated and should be continued as long as tumor targeted therapy is administered (both in control and intervention group). The RANO criteria is used in MRI assessment and for evaluation of progression
^28^.

After withdrawal of tumor target therapy no additional follow-up (including MRI) is planned within the context of this study, in order to minimize patient burden in the end of life setting. Safety assessment are according to the Common Terminology Criteria for Adverse Events (CTCAE) version 4.0
^29^. Survival is followed until death or 24 months post-inclusion.

***Data management*.** Data will be recorded in the web-based eCRFs (WebCRF 3.0) at The Unit for Applied Clinical Research at the NTNU. All data will be entered in the WebCRF 3.0 at the local study site. All electronic patient information is handled using a study participation number that is not logically connected to any personal data. It is possible to manually “decode” back to personal data using a name list stored securely at the respective study sites.

All data entered into the WebCRF are stored at two separate servers at NTNU. These servers are protected by the general firewall at the university and then by another firewall dedicated to protect clinical research data. The server that stores the data is not the same server as the one in contact with the Internet. There are several further safety measures not to be exposed. There are backups taken every 24-hour throughout the years. The responsibility for this system lies with the Unit for Applied Clinical Research at NTNU.

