## Discussion

This study investigates the role of DSF-Cu in recurrent glioblastoma. To our knowledge this is the first planned, randomized controlled trial with DSF-Cu in glioblastoma. The results from this trial will consequently serve as preliminary evidence of the future role of DSF-Cu in glioblastoma treatment as well as to serve as a basis for power estimations in future studies on the same topic.

The study has several pragmatic features, including an open design and a patient centered primary end-point
^33^. Due to the nature of our study end-point, we need to recruit more patients than if we had chosen a surrogate marker which is more common in the phase II setting. Nevertheless, we believe that surrogate markers are less relevant in the setting of glioblastoma recurrence since survival is short and image interpretation and response assessment is difficult
^6,
28^. Consequently, the trial is best described as a phase II/III trial. Further, the trial is to a high degree integrated within the frame of regular clinical practice, reducing the need of extra resources and thereby cost
^33^. The study will thus reflect clinical practice and the little deviation from everyday practice also reduce patient burden.

It may be a personal sacrifice for some patients to abstain from alcohol intake completely. Nevertheless, DSF has a well-known risk profile and the major risks of treatment with 400 mg DSF daily is mainly associated with lack of compliance with respect to alcohol intake and infrequently serious idiosyncratic hepatitis may be seen. In addition, there is a risk of neuropathy that is reversible upon drug discontinuation
^9^. In sum, the risks of DSF-Cu, also combined with chemotherapy, are presumably limited
^9^. The potential benefit lies in improved response to treatment.

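### The text sets blood and liver monitoring every 4–6 weeks with no time limit, but after month 12 Table 2 schedules samples only about every 13 weeks

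*Protocol article*

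**What the plan says.** The rule in Participant timeline reads: "hematological status and liver function will be monitored as long as patients are on active treatment every" 4–6 weeks. The exact interval is left to the chemotherapy regimen, Table 2 is cited, and no calendar limit is given.

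Table 2 marks blood samples at screening and in both visit columns. The monthly column lists months 1, 2, 4, 5, 7, 8, 10 and 11. The three-monthly column lists months "3,6,9,12,15,18,21,24". Two footnotes bear on the point:

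- On blood samples: "Blood samples as indicated here relevant as long as on active treatment and includes" the hematology and liver panel.
- On visit spacing: "The interval for patients treated with lomustine/PCV is 6 weeks, while 4 weeks is clinical routine in the case of temozolomide".

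Other parts of the article set the context:

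- Data collection: "Patients will be in the trial for a maximum of 24 months or until death", with Table 2 cited as the study schedule.
- Interventions: DSF-Cu carries on when chemotherapy is changed or paused.
- Data collection, on MRI: scanning may run to 24 months, and patients on DSF-Cu alone after progression are foreseen.
- Discussion, on disulfiram: "infrequently serious idiosyncratic hepatitis may be seen".

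**The concern.** The sentence and the table it cites give different monitoring intervals for the same patients after month 12. The footnote on blood samples limits them to patients on active treatment, which is the group the sentence describes. The later table entries therefore cannot be read as a lighter schedule for patients who have stopped treatment.

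What is at stake is how often a recognised liver risk is checked in year two, and whether all eight centers check it at the same frequency. Safety is a secondary end-point, compared as a composite of grade 3 to 5 toxicities, and a laboratory abnormality can be graded only if a sample is drawn. The consequence is confined to late safety data.

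**Working it through.** **Inputs.** The interval of 4–6 weeks comes from Participant timeline, the visit months from Table 2, and the 24-month maximum from Data collection.

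**Step 1: the article's own figure.** Participant timeline says of the two regimens that "this may lead to four additional observations in the temozolomide group compared with the lomustine/PCV group".

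- Over months 1–12: 12 monthly visits, and 12 / 1.5 = 8 visits at six-week spacing taken as 1.5 months. The difference is 12 − 8 = 4, which reproduces the stated figure.
- Over 24 months, had frequent visits continued: 24 and 24 / 1.5 = 16. The difference is 24 − 16 = 8, which does not.

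The stated four therefore fits frequent visits in the first year only. The short monthly column looks intended, not a truncated row.

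**Step 2: spacing in Table 2.** Merging the two columns gives visits at months 1 to 12 without a break, then 15, 18, 21 and 24: 12 in year one and 4 in year two.

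- Year-one gap: 1 month = 30.4375 / 7 ≈ 4.3 weeks.
- Year-two gap: 3 months = 3 × 30.4375 / 7 ≈ 13.0 weeks.
- Ratio to the text: 13.0 / 6 ≈ 2.2 and 13.0 / 4 ≈ 3.3.

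Month 12 is itself a sampling visit, so the intervals part company after month 12, not after month 11.

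**Step 3: checks in year two for a patient still on active treatment.**

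| Source | Checks in months 13–24 |
|---|---|
| Table 2 | 4 |
| Text, six-weekly | 12 / 1.5 = 8, or 52 / 6 ≈ 8.7 |
| Text, four-weekly | 12 (monthly), or 52 / 4 = 13 |

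**Step 4: how many patients.** The article gives no figure for treatment duration. Survival at 12 months bounds the number from above, but it needs a constant hazard, which the plan does not state.

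- Controls, from 50% dead within 8 months: 0.5^(12/8) = 0.354, and 0.354 × 71 ≈ 25.
- Controls, from 60% alive at 6 months: 0.60² = 0.36, and 0.36 × 71 ≈ 26.
- DSF-Cu, if the hypothesised 80% at 6 months is true: 0.80² = 0.64, and 0.64 × 71 ≈ 45. With no benefit the figure is that of controls, about 25 to 26.

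The number still on active treatment is at most the number alive, and how far below it cannot be derived.

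**The case against.** The best case for the plan is that nothing conflicts. Table 2 is labelled schematic. Its month numbers are already nominal, because a six-weekly patient cannot attend at every listed month. The sentence is explicit about interval and duration. A site can keep three-monthly trial visits in year two and draw extra bloods with chemotherapy, and the full protocol behind this article may settle the matter.

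Part of this stands. A reader might infer that the two instructions cannot both be followed. That goes too far: nothing in the table forbids extra samples, so a site could satisfy both by adding draws. It is also unknown whether the full protocol or the eCRF carries the same mismatch.

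The rest does not remove the point. The footnote ties samples to the visits as shown, and the spacing footnote adds none after month 11. Chemotherapy bloods cannot be assumed for a patient on DSF-Cu alone, and an interval that depends on the chemotherapy regimen does not tell a site what to do for that patient.

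Two further inferences are tempting but unsupported:

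- **That toxicity, compliance and discontinuation checks conflict in the same way.** The 4–6 week sentence covers only hematology and liver function. For visits in general, text and table agree, as Step 1 shows.
- **That about 25 and 45 patients would be affected.** These are survivors, not patients on treatment. They rest on a constant hazard, and the 45 also requires the hoped-for benefit to be real.

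Randomization is stratified by center, so differing site habits would not by themselves favor one arm.

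**Conclusion.** The text and Table 2 disagree on blood and liver monitoring after month 12: about 8 to 13 checks in year two by the sentence, 4 by the table, with gaps two to three times as long. This follows from visit counts alone and needs no survival assumption.

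It applies only to patients still on active treatment after month 12, an unknown number and probably a minority, since the article cites half of lomustine-treated patients dying within 8 months. The primary end-point is reached before the discrepancy begins, and neither the sample size nor the primary analysis depends on it. It is an internal inconsistency in safety monitoring that should be corrected. It does not threaten the trial's main conclusion.

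**What to change.** Reconcile three items so that they state one blood and liver schedule after month 12 for patients on active treatment: the monitoring sentence in Participant timeline, Table 2 with its blood-sample footnote, and the eCRF visits. State expressly what applies to a patient on DSF-Cu without chemotherapy. Either the table or the sentence can be changed; the clinical team decides which interval holds. The toxicity, compliance and discontinuation rows need no change on this ground.

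The cost is one correction to the table or text and a check of the eCRF visit structure. Recruitment was still open, with 36 patients randomized by October 2018, so the correction could still reach most of the planned 142.
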